### 2.4. Diagnostic Criteria

The diagnostic criteria for ischemic stroke (cerebral infarction) are as follows [38]: (1) most acute onset occurs in the static state, as dynamic onset patients are more common in cardiogenic cerebral infarction, and some cases may have transient cerebral ischemia attacks before onset; (2) aggravation or fluctuation is present; (3) clinical manifestations depend on the size and location of the infarct focus, mainly the symptoms and signs of focal neurological deficits, such as hemiplegia, paresthesia, aphasia, and ataxia, with some patients having headaches and vomiting, in coma, and others with whole-brain symptoms; and (4) there is confirmation via brain CT or MRI.

#### 2.4.1. Inclusion Criteria

The inclusion criteria for patients with stroke are as follows: (1) diagnosis of ischemic stroke confirmed by brain CT or MRI; (2) left cerebral ischemia (including the stroke patients with anterior and posterior circulation infarction) with right limb hemiplegia; (3) first-ever clinical stroke occurring between 2 weeks and six months; (4) aged between 30 and 70 years; (5) stable medical condition, Brunnstrom stages I–V; and (6) written informed consent to participate.

The inclusion criteria for healthy controls include the following: (1) can be matched to the patient's age, gender, and education; (2) has no acupuncture treatment in the last month; (3) has no history of head trauma, psychiatric disease, neurological disease, or physical activity disorder; (4) has no MRI contradictions; and (5) has provided written informed consent.

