### 2.2. Sample Size Calculation

Our primary outcome will be resting-state FC measured by rs-fMRI. Because millions of voxels are used to indirectly estimate the blood oxygen level-dependent (BOLD) signal and traditional power calculations are of no significance [32], we calculated the sample size according to the relevant published articles. Previous rs-fMRI study of the acupuncture mechanisms in stroke had a sample size of 20 cases for the healthy control group [33]. Moreover, a study on the effects of sample size on cerebral response to acupuncture with fMRI had shown that the imaging results in 17 healthy controls were similar to the results of studies with 21 cases [34], which may suggest that approximately 20 subjects maybe a relatively common choice in rs-fMRI studies after acupuncture. The sample size in acupuncture mechanism study using rs-fMRI with stroke patients typically ranges from a few cases to approximately 20 cases [33, 35–37]. Because this trial is a neuroimaging study, the primary outcome will be based on the subjects' MRI image processing, and patients with left cerebral ischemia accompanied by right limb hemiplegia will be enrolled in this study so as to ensure the relative consistency of cerebral ischemia lesions and reveal the neuroimaging mechanism more regularly.

Under the condition of left brain ischemia stroke with right limb hemiplegia in this study, we plan to enroll 20 patients diagnosed with ischemia stroke in each patient group (20 in the experimental group and 20 in the control group) and 20 healthy volunteers in the healthy control group.

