### 2.5. Randomization and Allocation

After meeting the selection criteria, 40 eligible patients will be randomly assigned into either the experimental group or the control group at an allocation ratio of 1 : 1 after signing written informed consent forms. The random sequence will be created by a third-party professional statistician of Shenzhen University using STATA 12.0 software (StataCorp, Texas, USA). The randomization list will only be seen by this research coordinator and will be concealed from other study personnel. Participant assignments will be hidden using sequentially numbered, opaque, sealed envelopes. The research coordinator that assigns the groups will not participate in the patients' inclusion, the subsequent trial process, or the assessment of results.

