Studies have found that abnormal brain structures and functions exist in patients after stroke compared with age- and gender-matched healthy controls [53, 54]. In this trial, we will aim to investigate the neuromodulatory effect of sensorimotor network FC of temporal three-needle therapy for ischemic stroke patients with motor dysfunction. First, we will compare the differences in baseline rs-fMRI metrics between the healthy subjects and the stroke patients to confirm the difference between the healthy subjects and stroke patients. Second, to determine the difference due to the temporal three-needle treatment, we will compare the changes in the rs-fMRI metrics between the experimental group and the control group to demonstrate whether motor function alteration is related to brain functional neuroplastic changes after temporal three-needle treatment. Although a large number of studies on the use of temporal three-needle therapy for the treatment of motor dysfunction, speech disorders, dysphagia, and depression after stroke have indicated clinical behavioral effects [11, 14–18], to the best of our knowledge, our study will be the first randomized neuroimaging trial with both a positive control group and a healthy control group to examine the actual effects by means of rs-fMRI.

This study has several strengths. First, the implementation of rigorous randomized, patient-assessor blind, controlled, neuroimaging trial will provide visual and objective evidence about how temporal three-needle treatment improves motor dysfunction in ischemic stroke patients. Second, the combined assessments of rs-fMRI and behavioral data will be used to identify the neuromodulatory effects of temporal three-needle therapy in stroke patients. Third, research based on the FC within the sensorimotor network, and between the sensorimotor network and nonmotor network, is better for understanding the mechanism of temporal three-needle therapy in stroke according to the “scalp-cortex corresponding theory.”

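### The stated between-arm analyses leave out time since stroke onset and lesion territory despite wide entry criteria; adjusting for onset time would recover precision at little cost

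*Protocol article*

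**What the plan says.** All references are to the protocol article.

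- **Entry.** Section 2.4.1 takes patients with "first-ever clinical stroke occurring between 2 weeks and six months" and with "left cerebral ischemia (including the stroke patients with anterior and posterior circulation infarction) with right limb hemiplegia". Severity is also broad: "stable medical condition, Brunnstrom stages I–V".
- **Aim of the left-sided restriction.** Section 2.2 limits entry to left-sided lesions "so as to ensure the relative consistency of cerebral ischemia lesions and reveal the neuroimaging mechanism more regularly".
- **Size.** Section 2.2 plans "20 in the experimental group and 20 in the control group". The number follows precedent; no effect size, SD or power is given.
- **Allocation.** Section 2.5 has patients "randomly assigned into either the experimental group or the control group at an allocation ratio of 1 : 1", using a computer-generated sequence and sealed envelopes. No stratification factor is named.
- **Imaging analysis.** Section 2.11.1 describes ICA, FDR correction and Pearson correlation. The Discussion adds that "we will compare the changes in the rs-fMRI metrics between the experimental group and the control group". No covariate is named in either place.
- **Clinical analysis.** Section 2.11.2 gives FMA and MBI a repeated-measures ANOVA with group, time and interaction effects, again without a covariate. Baseline characteristics are tested between arms, but nothing is said to follow from a difference. A significant primary difference is read as superiority.

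**The concern.** The primary outcome is change in FC over two weeks. A patient entering at two weeks and one entering near six months may be at different points of natural recovery, and infarct territory may matter too. The article gives no figure for either influence, so their strength is an assumption here.

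To the extent that such a factor predicts change, leaving it out of the between-arm model keeps its variance in the error term. With 20 per arm, chance can also place noticeably more early patients in one arm, and an unadjusted comparison then carries part of that difference into the treatment contrast. In a 40-patient trial with an active comparator, avoidable noise is worth removing, and the main factor is already recorded: onset time must be known to apply inclusion criterion (3).

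**Working it through.** The plan has no figure of its own to reproduce, because Section 2.2 gives no power calculation. The checks use 20 per arm (Section 2.2), two-sided 0.05 (Section 2.11.2) and an onset window of 2 to about 26 weeks (Section 2.4.1; 26/2 = 13-fold). The early/late split, the distribution of onset times, the variance explained (R²) and the effect size are assumptions.

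**1. Chance imbalance in a binary factor.** With K early patients among 40 and 20 per arm, the number early in one arm is hypergeometric.

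| K early of 40 | Arms differ by ≥4 | Arms differ by ≥6 |
|---|---|---|
| 20 | 34.3% | 11.3% |
| 12 | 30.1% | 8.2% |
| 8 | 23.5% | 4.4% |

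**2. Chance imbalance in onset time.** If onset is uniform over 2–26 weeks, the SD is 24/√12 = 6.93 weeks. The SE of the difference in means is 6.93 × √(2/20) = 2.19 weeks. The probability that the arms differ by 3 or more weeks is 2 × [1 − Φ(3/2.19)] = 17%.

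**3. How far an imbalance moves the contrast.** A half/half factor with variance share R² separates early from late by 2√R² total SDs. The SE of the arm contrast is √(2/20) = 0.316 SD.

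- 12 versus 8 early (20 points): 0.20 × 2√0.10 = 0.13 SD at R² = 10%, and 0.20 × 2√0.30 = 0.22 SD at R² = 30%. These are 0.4 and 0.7 of an SE.
- 13 versus 7 early (30 points): 0.19 SD and 0.33 SD, or 0.6 and 1.0 of an SE.
- An unadjusted test needs about 0.64 SD for significance. The effect detectable with 80% power is (1.960 + 0.842) × 0.316 = 0.89 SD.

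**4. Error rate and power.** These come from simulation: 20,000 runs per setting, a half/half factor, unadjusted t-test against ANCOVA.

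| R² | Type I error, unadjusted, given imbalance ≥6 | Power at 0.8 SD, unadjusted | Power at 0.8 SD, adjusted |
|---|---|---|---|
| 0 | 6% | 0.69 | 0.68 |
| 10% | 8% | 0.70 | 0.73 |
| 25% | 14% | 0.69 | 0.80 |
| 40% | 20% | 0.68 | 0.88 |

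Over all allocations, unadjusted type I error was 4.8–5.3% and adjusted about 5%, whatever R² was. When allocation was stratified but the analysis was not adjusted, type I error fell to 4.0%, 2.4% and 1.1% at R² of 10%, 25% and 40%. The test becomes conservative.

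**5. Precision gained.** With one covariate, the variance of the arm contrast is multiplied by about (1 − R²) × 38/37. This gives 0.924, 0.822 and 0.719 at R² = 10%, 20% and 30%, reductions of 8%, 18% and 28%. If a second covariate is added and explains nothing further, the multiplier is (1 − R²) × 38/36 = 0.950, 0.844 and 0.739, reductions of 5%, 16% and 26%.

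**The case against.** A reader might infer that spontaneous recovery could pass for a treatment effect, so that the primary comparison is biased. The documents do not support that. Both arms are randomised concurrently and receive the same background drugs and rehabilitation (Section 2.1), so recovery is expected in both. Chance imbalance is already covered by the 5% error rate. A 12-versus-8 split moves the contrast by less than one SE, which is far from producing a significant result alone. This objection stands, and it confines the point to precision and to allocations that happen to be unbalanced.

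A reader might also infer that Section 2.4.1 contradicts Section 2.2. It does not. Section 2.2 claims only relative consistency, and the side restriction is kept. Admitting both circulations does mean that the claim is best read as one about side.

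Finally, the article is a condensed account. It does not state that the imaging comparison is unadjusted or that allocation is unstratified, and covariates may be set out in a full protocol or analysis plan that is not shown. This weakens any charge of omission, and the point should not be put as one. What remains is that the analyses, as stated for both imaging and clinical outcomes, make no use of a factor that is known at entry and varies widely by design.

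**Conclusion.** The point holds as a recommendation on efficiency and robustness. The between-arm analyses as stated leave out time since onset and lesion territory in a population chosen to span 2 weeks to six months and both circulations. Validity over all allocations is intact, with type I error near 5%.

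The expected gain from adjusting for onset time is a reduction of about 8–28% in the variance of the arm contrast if it explains 10–30% of the variance in change. If it explains nothing, the loss is negligible (power 0.68 against 0.69 at 0.8 SD). Adjustment also protects against the roughly one allocation in nine (11%, if half the patients are early) in which the arms differ by 6 or more early patients.

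These sizes rest on assumed values of R², the early/late split and the effect, none of which the article gives. The power figures use a binary factor and a single continuous outcome, so they only indicate what to expect for a voxelwise FC analysis. No separate size can be given for lesion territory, because its mix among patients is unknown.

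**What to change.** 1. Prespecify time since stroke onset, as a continuous variable, as a covariate in the between-arm models for FC, ReHo, ALFF, FMA-UL and MBI. Date this before unblinding. Section 2.6 discloses the code only after the statistical analysis is complete, so it should also precede the first comparison of groups A and B.
2. For FMA and MBI, let onset time act on change: either as a covariate in an analysis of change or as a covariate-by-time term in the repeated-measures model. A covariate main effect alone leaves the group-by-time contrast untouched.
3. Add lesion territory (anterior or posterior) only if both categories are adequately represented, judged without reference to outcome. It should be readable from the diagnostic imaging and the structural scans in Section 2.9.
4. Limit the consistency statement in Section 2.2 to lesion side.
5. Stratifying the remaining allocations by onset time is optional. Recruitment is under way (Section 2.14), so its value depends on how many patients are already randomised. It should be done only if the factor is also in the analysis model, since otherwise the test becomes conservative.

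The cost is one degree of freedom per covariate out of about 38 and a short amendment to the analysis text. Onset time needs no new data collection.

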#### 2.4.2. Exclusion Criteria

The exclusion criteria are as follows: (1) a history of previous traumatic brain injury, tumor, or epilepsy; (2) bilateral hemiplegia; (3) critical organ failure, such as heart, lung, liver, and kidney failure; (4) severe cognitive impairment and inability to cooperate; (5) claustrophobia, wearing a pacemaker, intracranial metal implants, or skull defects; (6) severe cervical lesions including severe cervical spinal stenosis and cervical instability; (7) women who are pregnant or lactating; (8) contradictions for MRI scans; (9) currently participation in another clinical trial that would affect the evaluation results of this study; or (10) fear of needling, needle phobia, and fainting with needles.

#### 2.4.3. Dropout Criteria

During the trial period, participants meeting the following criteria will be excluded from the study: (1) occurrence of serious adverse events; (2) missing more than 3 of 10 acupuncture treatment sessions; (3) important violations in the protocol implementation; or (4) withdrawal from the study in light of the participants being unwilling to continue.

### 2.5. Randomization and Allocation

After meeting the selection criteria, 40 eligible patients will be randomly assigned into either the experimental group or the control group at an allocation ratio of 1 : 1 after signing written informed consent forms. The random sequence will be created by a third-party professional statistician of Shenzhen University using STATA 12.0 software (StataCorp, Texas, USA). The randomization list will only be seen by this research coordinator and will be concealed from other study personnel. Participant assignments will be hidden using sequentially numbered, opaque, sealed envelopes. The research coordinator that assigns the groups will not participate in the patients' inclusion, the subsequent trial process, or the assessment of results.

### 2.6. Blinding

The trial will be conducted using a patient-assessor blind design. The patients, assessors, and statisticians will not be aware of which group the patients are in. They will only be told whether data will belong to group A or group B, but they will not be aware of which group is the experimental group or the control group. Furthermore, they will not even know whether the trial is designed to be a noninferiority trial, an equivalent trial, or a superiority trial, thus avoiding human factors affecting the results of the data analysis.

Regarding acupuncture implementation, acupuncture doctors cannot be blinded, so unblinded acupuncture doctors will apply the acupuncture intervention depending on the patients' intervention arm.

The blind method will be applied throughout the whole study process. A member of the trial staff will supervise the process of blind implementation and will disclose the blind code after the statistical analysis is completed. Unblinding will be considered only in a critical medical emergency.

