### 2.8. Outcome Assessment

The outcome measurements include functional connectivity (FC), regional homogeneity (ReHo), amplitude of low-frequency fluctuations (ALFF), the Fugl–Meyer assessment of upper limb (FMA-UL), the modified Barthel Index (MBI), and adverse events. FC, ReHo, and ALFF will be measured by rs-fMRI. The FMA-UL, MBI, and adverse events (AEs) will be assessed by three experienced rehabilitative assessors.

Additionally, the study duration will be 2 weeks. Outcomes will be assessed at baseline and after 2 weeks of intervention. Each subject will have the same assessor for their pre- and posttreatment evaluations.

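### As worded, Section 2.6 gives the A/B group label to patients and outcome assessors as well as statisticians, so one disclosure could decode the arm of all 40 patients

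*Protocol article*

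**What the plan says.** Section 2.6 sets the rule in consecutive sentences. It first names the blinded parties: "The patients, assessors, and statisticians will not be aware of which group the patients are in". It then says what they receive: "They will only be told whether data will belong to group A or group B". It then says what is withheld: "they will not be aware of which group is the experimental group or the control group".

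Other sections bear on this:

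- Section 2.5, on concealment: "The randomization list will only be seen by this research coordinator and will be concealed from other study personnel".
- Section 2.8, on who scores: "The FMA-UL, MBI, and adverse events (AEs) will be assessed by three experienced rehabilitative assessors". It adds: "Each subject will have the same assessor for their pre- and posttreatment evaluations".
- Section 2.6, on breaking the blind: "Unblinding will be considered only in a critical medical emergency".
- Section 2.2, on numbers: "20 in the experimental group and 20 in the control group", so 40 patients in all.

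**The concern.** A coded label is ordinary practice for a statistician, who must compare two groups without knowing which is which. An assessor who scores one patient at a time has no use for it. Once assessors hold the letter, they know the true grouping of their patients and lack only the names of the two arms. One piece of information about one patient supplies those names.

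FMA-UL items are scored on a three-level judgement of how far a movement is performed (Section 2.8.2), so an assessor's belief about the arm can influence the score. The FMA-UL and MBI changes are compared between arms (Section 2.11.2). They also supply the behavioural side of the second objective, which relates connectivity change to behavioural change (Introduction, Section 2.11.1). The Discussion counts the blinding of patients and assessors among the strengths of the trial, so the blinding rule should support that claim.

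**Working it through.** The article gives no figure on this point, so there is nothing of its own to reproduce. The check is a reading of the text, a count, and an illustration under stated assumptions.

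**1. Who receives the label.** The pronoun that opens the second sentence of Section 2.6 has one antecedent: patients, assessors and statisticians together. The only thing withheld is the meaning of the letters. No other section restricts the label to the statistician or says that assessors work from unlabelled forms.

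**2. Comparison with Section 2.5.** The list is to be seen by the research coordinator only. A patient-by-patient A/B label is that list, up to a swap of the two letters. Giving it to assessors works against the concealment in Section 2.5.

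**3. Routes to a disclosure, all from the article.**
- The two treatments use different scalp sites (Sections 2.7.3 and 2.7.4), and patients feel the needling where it is done.
- The assessors of FMA-UL and MBI also assess adverse events (Section 2.8). Those foreseen in Section 2.13 include swelling from bleeding and a retained needle, either of which can show the site.
- Emergency unblinding is allowed (Section 2.6).

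**4. Exposure count.** Inputs: 20 patients per arm and two arms (Section 2.2).

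| What assessors hold | Patients decoded by one disclosure |
|---|---|
| Shared A/B label | 20 with that letter + 20 by elimination = 40 of 40 |
| Participant number only | 1 of 40 (2.5%) |

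In the second row, the other 39 patients split 20 and 19. A guess from the counts alone is then right 20/39 = 51% of the time. In the first row, a single assessor decodes every patient whose letter he or she has been given. The article does not say how patients are divided among the three assessors.

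**5. Illustration of the bias.** Let b be the score shift given to a patient believed to be in the experimental arm relative to one believed to be a control, and p the probability of guessing the arm correctly. Neither is in the documents. An experimental patient receives the shift with probability p and a control with probability 1 − p, so

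expected between-arm bias = p·b − (1 − p)·b = (2p − 1)·b.

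With the letters correctly decoded, p = 1 and the bias is b. The ratio of decoded to unlabelled bias is 1/(2p − 1):

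| Assumed p | Unlabelled bias | Ratio after decoding |
|---|---|---|
| 0.55 | 0.10b | 10 |
| 0.60 | 0.20b | 5 |
| 0.70 | 0.40b | 2.5 |

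The ratio shrinks as unlabelled guessing improves. Nothing in the documents says where p lies, or that b differs from zero.

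**The case against.** The strongest reply is that the authors meant ordinary coding for the analyst. The sentence speaks of data, not patients, and the paragraph ends by giving protection of the data analysis as its aim. Patients do not handle trial data, so the literal reading fits them poorly. Section 2.5 conceals the list and uses numbered sealed envelopes, and Section 2.6 has a staff member supervise the blinding. The layout of the assessment forms would normally be in the full protocol or the case report form, which are not shown. This may well be what was intended, and the article does not establish that labels reach the assessment room. But the written rule covers assessors, and for the person who produces a patient's score, a label on the data is a label on the patient. If the intention was narrower, the sentence needs the same correction.

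Several stronger readings are tempting and are not supported:

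- A reader might infer that patients learn which other patients are A or B. The text supports at most that each learns his or her own letter.
- A reader might infer a definite inflation of the treatment effect, or calculate how often an assessor would break the code by pooling guesses within a letter. That needs a guess rate, independent guesses and the number of patients per assessor, none of which the documents give. Without a true disclosure the letters could also be decoded the wrong way round, which would reverse the bias.
- A reader might infer that labels alone give the bias its direction. By the formula above, unlabelled guessing at better than chance biases in the same direction. The label changes the extent.
- A reader might infer that the trial's main result is compromised. The primary outcome is resting-state connectivity from MRI (Section 2.8.1), which these assessors do not score. Section 2.11.2 tests the secondary endpoints only if the primary is significant.

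It also stands that a patient can mention the needle site with or without a letter. And because both arms receive active scalp acupuncture, the size of b is uncertain.

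**Conclusion.** The point holds as a fault in a stated rule: Section 2.6 extends the A/B label to people who should not have it, and the rest of the article does not correct this. The firm part of its size is the count: one disclosure exposes 40 of 40 patients under shared letters, against 1 of 40 without them. This assumes that the rule is applied as written and that the disclosure reaches assessors who hold the letters. The multiplier of about 10 to 2.5 rests on an assumed guess rate of 55% to 70% and a common shift b. It illustrates the mechanism and does not estimate bias in this trial. The consequence is confined to the judgement-scored secondary outcomes and the behavioural half of the mechanism analysis. The change should be made because it lowers that risk at almost no cost.

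**What to change.** Reword Section 2.6 to state three things:

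1. Only the statistician receives the A/B code.
2. Patients and the assessors of FMA-UL and MBI receive no group label.
3. Assessment forms and scans carry only a participant number, and that number does not encode the group.

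The cost is a short change of wording and an unlabelled form, with no added staff or visits. Section 2.14 says the trial is still recruiting, so the change can protect the remaining assessments. If the forms already carry no letter, the edit only brings the text into line with practice. It limits a disclosure to the patient concerned but does not prevent that patient from revealing the needle site.
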